### Missing data

Missing data will be characterised in terms of amount and pattern at each planned analysis. For multivariable analyses, data missing at random (MAR) will be handled using multiple imputation by chained equations (MICE) with 20 imputed datasets pooled using Rubin's rules [42]. Complete-case analyses will serve as the primary approach and MICE results as sensitivity analyses. Where data missing not at random (MNAR) cannot be excluded (particularly for SDOH variables where “prefer not to answer” may be non-random), best-case and worst-case sensitivity analyses will be conducted [42].

Missing patient-reported outcome data and incomplete follow-up are anticipated to be the principal analytic challenges over the observation window to age 18, and are addressed by a pre-specified hierarchy of methods. At the item level, partially completed questionnaires will be prorated according to the developer’s published scoring rule, and scale scores will be set to missing where fewer than the minimum required items are available. At the visit level, longitudinal analyses of PRO scores will use linear mixed-effects models and generalised estimating equations, which retain participants with incomplete visit series and yield valid inference under a missing-at-random assumption [41]. For multivariable models requiring complete covariate vectors, multiple imputation by chained equations will be used, with the imputation model including the analysis model variables, the outcome, and auxiliary variables predictive of non-response (age band, distance from COCOE, deprivation quintile, language of administration, and number of previously missed appointments) [42].

As loss to follow-up and PRO non-response may both be informative, inverse probability of censoring weights estimated from these same predictors will be applied as a sensitivity analysis to the survival and longitudinal models [26,27]. Robustness to departures from the missing-at-random assumption will be assessed using pattern-mixture models in which imputed PRO scores are delta-adjusted by 0.2, 0.5, and 0.8 standard deviations in the unfavourable direction. The amount and pattern of missingness, by instrument, visit, and disease cohort, will be tabulated in every registry publication, and no outcome analysis will be reported without the accompanying completeness figures. A pre-specified threshold of more than 40% missingness for a given instrument at a given assessment point will preclude model-based inference for that instrument at that point, which will instead be reported descriptively.

This protocol paper has additionally been prepared with reference to the SPIRIT 2025 statement (Standard Protocol Items: Recommendations for Interventional Trials) [43], adapted for observational registry protocols. A completed SPIRIT checklist is provided as S1 File.

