## Statistical analysis

Analyses are pre-specified by objective as follows.

**Objective 1:** Incidence and clinical outcomes. Descriptive summaries of diagnosis, surgical procedures, and complication rates will be reported using means (SD) or medians (IQR) for continuous variables and frequencies (%) for categorical variables [39]. Time-to-event outcomes (e.g., first HAEC episode, reoperation) will be analysed using Cox proportional hazards regression. Where competing risks are present (e.g., death or transition to adult care prior to the event of interest), the Fine-Gray subdistribution hazard model will be applied [40]. Candidate predictors for each time-to-event model are pre-specified as: diagnosis type, Krickenbeck category or aganglionosis length, age at index repair, sex, syndromic status, and area-level deprivation quintile.

**Objective 2:** Patient-reported outcomes. Longitudinal PROM/PREM data collected across multiple clinic visits will be analysed using linear mixed-effects models (for continuous scores) or generalised estimating equations (GEE; for binary or count outcomes), with an unstructured or autoregressive covariance structure selected by the Akaike Information Criterion [41]. Cross-sectional group comparisons at a single timepoint will use chi-square or Fisher's exact tests (categorical) and independent-samples t-tests or Mann-Whitney U tests (continuous), as appropriate.

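### Unweighted GEE is credited with validity under missing at random, and as worded AIC selects its covariance structure; neither holds for GEE, though only binary and count PROM/PREM outcomes are affected

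*Protocol article*

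**What the plan says.** All references are to the Protocol article.

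- **Statistical analysis, Objective 2.** Continuous PROM/PREM scores go to linear mixed-effects models. The alternative is "generalised estimating equations (GEE; for binary or count outcomes"). The same sentence then continues "with an unstructured or autoregressive covariance structure selected by the Akaike Information Criterion".
- **Missing data, visit level.** The text says that "longitudinal analyses of PRO scores will use linear mixed-effects models and generalised estimating equations". It then makes one claim for the two methods together, describing them as approaches "which retain participants with incomplete visit series and yield valid inference under a missing-at-random assumption".
- **Missing data, imputation.** "For multivariable models requiring complete covariate vectors, multiple imputation by chained equations will be used". Complete-case analysis is primary for multivariable analyses, with imputation as a sensitivity analysis. The auxiliary predictors of non-response are "age band, distance from COCOE, deprivation quintile, language of administration, and number of previously missed appointments".
- **Missing data, weighting.** "inverse probability of censoring weights estimated from these same predictors will be applied as a sensitivity analysis", covering both survival and longitudinal models. The section adds delta-adjusted pattern-mixture models. It also bars model-based inference for an instrument at any assessment point with more than 40% missing.
- **Survey administration and burden mitigation.** Expected instrument completion is 70–80% per visit.

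**The concern.** A mixed model fitted by likelihood uses the joint distribution of the repeated scores. If that model is right, missingness that depends on earlier observed scores can be ignored. GEE specifies only the marginal mean and a working correlation. Its unweighted estimating equation is guaranteed to have mean zero only when missingness does not depend on outcomes, given the covariates in the model. If children who did well (or badly) at one visit are likelier to skip the next, the data can be missing at random and ordinary GEE can still be biased.

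AIC is computed from a likelihood. GEE has none, so AIC cannot rank its working correlations; QIC is the usual counterpart. The choice matters here because the bias depends on which of the two permitted structures is used.

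At stake is how longitudinal binary and count PROM/PREM results are read. They would be presented as valid under MAR when they are not in general, in a registry that itself expects loss to follow-up and non-response to be possibly informative.

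**Working it through.** The plan gives no figure for these analyses, so there is none to reproduce. All drop-out settings below are assumptions.

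**1. The mechanism by hand.** Assume a binary outcome with true prevalence 0.40, and drop-out before the next visit of 10% after outcome 1 and 35% after outcome 0.
- Retained: 0.40 × 0.90 + 0.60 × 0.65 = 0.36 + 0.39 = 0.75, so 25% are missing, within the 20–30% implied by 70–80% completion.
- Share of the retained whose previous outcome was 1: 0.36 / 0.75 = 0.48, not 0.40.
- A common weight of 1/0.75 leaves this at 0.48.
- Weights of 1/0.90 and 1/0.65 give 0.36/0.90 = 0.40 and 0.39/0.65 = 0.60, which restores 0.40.

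Only weights that carry information on the earlier outcome repair the imbalance.

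**2. The same drop-out in fitted models.** Settings: n = 400, 4 visits, exchangeable latent correlation 0.6, monotone drop-out; 200 replicates (150 for the autoregressive and unstructured fits). The true prevalence at visit 4 is 0.40.

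| Drop-out | Analysis | Visit-4 estimate | 95% CI coverage |
|---|---|---|---|
| Unrelated to outcome | Unweighted, independence | 0.404 | 0.945 |
| MAR | Autoregressive | 0.453 | 0.67 |
| MAR | Unstructured | 0.393 | 0.95 |
| MAR | Independence, weights without the outcome | 0.496 | 0.295 |
| MAR | Independence, weights with the previous outcome | 0.399 | 0.955 |

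This shows that the bias exists, not how large it would be here. Retention under MAR was 0.751, 0.568 and 0.436 at visits 2 to 4, so 24.9%, 43.2% and 56.4% were missing. Visits 3 and 4 exceed the 40% limit and would be reported descriptively. At visit 2, within the limit, the autoregressive estimate was 0.405, an error of 0.5 points.

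**3. Size within the 40% limit.** Settings: random-intercept logistic outcome, monotone MAR drop-out, n = 200,000.
- 4 visits, drop-out 20% after a good score and 5% after a poor one, 31.5% missing at the last visit: truth 52.9%, autoregressive 50.5%, unstructured 52.9%. Autoregressive error: 52.9 − 50.5 = 2.4 points.
- 5 visits, drop-out 18% and 2%, 32.5% missing: truth 56.1%, autoregressive 52.0%, unstructured 56.1%. Autoregressive error: 56.1 − 52.0 = 4.1 points.
- A 3:1 drop-out ratio scaled to 22–28% missing: autoregressive error about 1.5–2.0 points, unstructured within 0.1.
- Non-monotone missingness of 20–26% per visit depending on the previous outcome (only approximately MAR): autoregressive error about 0.4–0.6 points.

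Over monotone settings with about 27–34% missing at the last visit, the autoregressive error is about 1.6–4 points, and unstructured stays within about 0.3.

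**4. Do the other provisions repair it?** The weighting "will be applied as a sensitivity analysis to the survival and longitudinal models", so the main GEE is unweighted. Its predictors most naturally refer back to the auxiliary list, which names no earlier score. Imputation is tied to incomplete covariates and is not stated for outcomes missed at a visit before GEE. The delta adjustments probe departures from MAR; they do not correct an analysis that can already be biased under MAR.

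**The case against.** The best case for the plan has five parts.

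- **No named outcome uses GEE.** Table 2 assigns the primary outcome, HAEC and reoperation to survival models, HAQL and TRAQ to linear mixed models, and loss to follow-up to logistic regression. This stands and bounds the consequence.
- **Large biases arise only where the plan would not model.** A reader might infer an error of five points or more: with 30% and 10% drop-out over five visits, autoregressive GEE gave 52.1% against a true 57.8%. Drop-out that heavy leaves nearly 60% missing at the last visit, above the 40% limit. The 70–80% completion figure is also a per-visit rate, not a drop-out rate that compounds. This stands. Independence working correlation is not a permitted option either, so its larger bias does not count against the plan.
- **The AIC clause may be meant for the mixed models alone.** Covariance structure is mixed-model language, and a condensed article may merge two methods in one clause. That is possible. The sentence as written covers both, so it needs rewording either way.
- **The weights may help.** A reader might infer that they cannot correct outcome-dependent drop-out at all. That is too strong: missed appointments, distance or deprivation may correlate with the child's status, and the imputation model whose predictors are reused does include the outcome. What can be said is that no earlier score is listed, so correction may be incomplete.
- **There are other safeguards.** Delta adjustment and mandatory completeness tables mean the results would not go out unexamined. This is true, but neither makes the MAR sentence correct for GEE.

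**Conclusion.** The MAR statement is wrong for unweighted GEE, and the AIC rule does not apply to GEE as worded. These are errors in what the protocol states, not details left to a statistical analysis plan. Their reach is limited to binary and count PROM/PREM outcomes, none named in Table 2; the documents do not support reading this as a threat to the primary outcome, HAQL or TRAQ.

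A reasonable size is a bias of about 1.6–4 percentage points if the autoregressive structure is used, drop-out is monotone and depends on the previous outcome, and about 27–34% are missing at the last visit. Non-monotone missingness may give less. The direction depends on who drops out. The unstructured option was nearly unbiased in these settings, but that is not guaranteed and the plan does not fix it. The size rests on assumed drop-out rates and correlation; that GEE lacks general MAR validity does not. The correction should be made, and it can be narrow.

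**What to change.** 1. In Missing data, limit the MAR sentence to the linear mixed models, and state that unweighted GEE needs missingness unrelated to outcomes given the modelled covariates.
2. In Statistical analysis, Objective 2, limit AIC to the mixed models. For GEE, fix the working correlation in advance or choose it by QIC, with robust standard errors.
3. For binary and count outcomes, make the primary analysis either GEE with inverse-probability weights that include the last observed score, or GEE after multiple imputation of missed-visit outcomes using earlier scores. Both keep the marginal estimand; a generalised linear mixed model would change it to a subject-specific one.
4. Add the last observed score to the weight model now listed for the sensitivity analysis.

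The cost is a wording change, modest extra analysis work and slightly wider intervals from the weights. No new data are needed, because earlier scores are already part of the repeated PROM/PREM collection, and Study timeline and milestones states that no formal analysis has yet been done.

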The primary outcome is time to achievement of fecal continence from the date of definitive surgical repair, analysed as a time-to-event outcome. For participants with ARM, continence is assessed using the Baylor Continence Scale (BCS) [16], with social continence defined as no soiling episodes in the preceding 4 weeks per published BCS criteria, completed by the parent or caregiver proxy up to age 11 and by self-report from age 12. For participants with HD, continence is assessed using the Bowel Function Score (BFS) [17], with social continence defined as a BFS score ≥ 17, administered to the parent or caregiver proxy up to age 11 and by self-report from age 12. Both instruments are administered at every annual clinic visit beginning at age 3 years. The earliest clinically meaningful assessment for continence is age 3, consistent with normal developmental milestones for voluntary bowel control. Participants will be censored at age 18, death, transition to adult care, or loss to follow-up, whichever occurs first.

Pre-specified secondary outcomes, listed in priority order, are: (1) Hirschsprung-associated enterocolitis (HAEC), defined as at least one physician-confirmed episode meeting the Ruttenstock diagnostic criteria and requiring medical treatment, assessed at each annual visit [20]; (2) reoperation rate, defined as any unplanned surgical return to the operating room following index repair, assessed cumulatively; (3) disease-specific quality of life, measured using the HAQL [18] at ages 6, 10, and 14 years using age-appropriate versions; (4) transition readiness, assessed at ages 14 and 17 years using the validated Transition Readiness Assessment Questionnaire (TRAQ) [19], and (5) loss to follow-up rate, defined operationally in the Loss to Follow-Up section. Each secondary outcome will be reported descriptively and, where the events-per-variable threshold is met (see Sample Size section), included as an endpoint in pre-specified multivariable analyses with the analytic role specified in the Statistical Analysis section.

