### Loss to Follow-Up

A participant will be considered lost to follow-up if there has been no clinic encounter, completed survey, or successful contact (by telephone, email, or mail) for 18 or more consecutive months in a participant aged under 18 years who has not yet transitioned to adult care or withdrawn from the registry.

When a participant misses a scheduled visit without prior notification, the research assistant will initiate a standardised re-contact sequence: (1) two phone call attempts within 2 weeks; (2) email or written letter within 4 weeks, if contact information is on file; and (3) two further phone call attempts at 3 months. If no successful contact is made after this full sequence, the participant will be flagged as lost to follow-up in REDCap with the date of last confirmed contact recorded. All contact attempts and outcomes will be logged prospectively.

Rates and timing will be reported descriptively at each annual analysis. In survival and longitudinal analyses, the loss will be treated as censoring at the date of last confirmed contact. The potential impact of informative (non-random) censoring will be examined using inverse probability weighting (IPW) as a sensitivity analysis [26,27]. Factors independently associated with the loss will be examined using logistic regression (ever-lost vs retained) as a secondary analysis, with candidate predictors pre-specified to include: diagnosis type, age at enrollment, sex, aganglionosis length or ARM Krickenbeck category, area-level deprivation quintile, and distance from COCOE.

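### The censoring weights omit continence history and severity, so they test informative dropout for time to continence only as far as five demographic and attendance predictors act as proxies

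*Protocol article*

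**What the plan says.** All references are to the protocol article.

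- **Loss to Follow-Up** sets the handling: "In survival and longitudinal analyses, the loss will be treated as censoring at the date of last confirmed contact". It then announces the check, without naming covariates for the weights: "The potential impact of informative (non-random) censoring will be examined using inverse probability weighting (IPW) as a sensitivity analysis".
- **Missing data** gives the reason, "As loss to follow-up and PRO non-response may both be informative", and the method: "inverse probability of censoring weights estimated from these same predictors will be applied as a sensitivity analysis to the survival and longitudinal models".
- The list that this points back to closes the preceding paragraph of the same section: "auxiliary variables predictive of non-response (age band, distance from COCOE, deprivation quintile, language of administration, and number of previously missed appointments". There it is the last of three components of the imputation model.
- **Loss to Follow-Up** also lists candidate predictors for a separate logistic regression of loss: "diagnosis type, age at enrollment, sex, aganglionosis length or ARM Krickenbeck category, area-level deprivation quintile, and distance from COCOE".
- **Outcome measures** says of the BCS and BFS: "Both instruments are administered at every annual clinic visit beginning at age 3 years".

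**The concern.** Inverse probability of censoring weights remove only the part of the link between dropout and outcome that the covariates in the weight model explain. The five listed predictors describe where the family lives, its circumstances and its attendance. They say nothing direct about how the child is doing. If families leave because continence has been reached, or because it has not, the weights can miss that.

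The protocol's own list of candidate predictors of loss includes diagnosis and severity, yet the weights meant to address that loss leave severity out. Weighted and unweighted curves could then agree while both are biased, and the agreement would be reported as reassurance about the primary outcome.

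**Working it through.** **1. Which covariates the weights use.** The nearest antecedent of the back-reference is the auxiliary list, which is described as predicting non-response. It holds no BCS or BFS result, PRO score, Krickenbeck category, aganglionosis length, syndromic status or bowel-management status.

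**2. What else checks informative censoring of time to continence.**

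- Delta adjustment (Missing data) is applied to imputed PRO scores, not to censored continence times.
- Best-case and worst-case analyses (Missing data) are aimed mainly at social-determinant variables and are not specified for censored times.
- The Cox models (Statistical analysis, Objective 3) adjust for severity and syndromic status. The Kaplan-Meier curves and landmark proportions are split by disease only.

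The weights are thus the only named check for the curves and the landmark proportions.

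**3. The mechanism.** At visit t a child still followed has weight W(t) = product over k ≤ t of 1 / P(still followed at k | followed at k−1, not yet continent, covariates at k−1). The weighted hazard is h(t) = ΣW·event / ΣW over those at risk, and cumulative continence is 1 − Π(1 − h). This is unbiased only if, given the covariates in P, dropout is unrelated to later continence.

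**4. Illustration.** The documents give no expected loss rate and no strength of dependence, so every parameter is an assumption. There were 8 annual visits (ages 3 to 10) and n = 200,000. The score was 12 + 2.2 × latent function + 0.35 per year + noise (SD 1.2), with an event at a score of 17 or more. Dropout log-odds were −2.4 + 0.4Z − g × (last score − 13)/2.5. Z stands for the five listed predictors. Cumulative loss was 47-50%. Confirmation at a second visit and competing events were left out.

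| g | Correlation of Z with latent function (absolute) | Truth % | Unweighted % | Weights on Z % | Weights on Z and last score % |
|---|---|---|---|---|---|
| 0.4 | 0 | 23.6 | 26.7 | 26.9 | 23.6 |
| 0.4 | 0.3 | 23.8 | 27.9 | 26.6 | 23.7 |
| 0.4 | 0.6 | 23.8 | 29.1 | 25.8 | 23.8 |
| 0.8 | 0 | 23.9 | 30.3 | 30.7 | 23.8 |
| 0.8 | 0.3 | 23.5 | 31.1 | 29.8 | 23.5 |
| 0.8 | 0.6 | 23.6 | 32.3 | 27.9 | 23.6 |

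- Error left after weighting on Z: from 25.8 − 23.8 = 2.0 points to 30.7 − 23.9 = 6.8 points.
- Share of bias removed at correlation 0.6: (29.1 − 25.8)/(29.1 − 23.8) = 62% and (32.3 − 27.9)/(32.3 − 23.6) = 51%.
- Share removed at correlation 0.3: 1.3/4.1 = 32% and 1.3/7.6 = 17%.
- At correlation 0, weighting moves the estimate by 0.2 to 0.4 points while the bias is 3.1 to 6.4 points. This is the false reassurance.

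Other assumed settings bracket this. With a strong dependence of 0.9, Z unrelated to the score and a truth of 48%, Kaplan-Meier gave 55% or 41% depending on which children leave, weights on Z gave 55% or 40%, and adding the score gave 48% or 47%. With a weak dependence of 0.2 per SD, the bias was 2 points at zero correlation; at correlation −0.5, weights on Z cut it from 4.4 to 1.8 points.

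**5. PRO scores.** In a three-visit version (n = 6,000, true third-visit mean 65.7-66.2), the unweighted mean was 67.5-70.2, listed-type weights gave 67.4-69.3, weights that include the earlier score gave 65.7-66.2, and a random-intercept mixed model gave 65.7-66.6.

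**The case against.** Five points can be made for the plan.

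- **The listed predictors suit the bias that the protocol fears.** A reader might infer that the bias called most threatening under Strengths and limitations goes unchecked. The text does not support that. It describes families who live far away, lack stable housing or a telephone, or speak neither French nor English. Distance, deprivation, language and missed appointments measure that mechanism directly or by proxy. Loss related to the child's own continence or severity is a different mechanism.
- **The weights are not powerless.** A reader might infer that they cannot correct outcome-related dropout at all. The same section of the protocol links better resources with better measured outcomes, and under such a link the simulation shows partial correction. This stands.
- **PRO scores are largely covered.** Likelihood-based mixed models allow dropout that depends on earlier observed scores, and the delta adjustment probes departures from that. This stands, except for unweighted GEE, which the protocol credits with the same validity but which does not have it in general.
- **Severity is in the Cox models.** This stands for the adjusted models, not for the Kaplan-Meier and landmark estimates.
- **The back-reference may cover the whole imputation model.** The imputation sentence reads "with the imputation model including the analysis model variables, the outcome, and auxiliary variables predictive of non-response", so the weights might be meant to include all three components. This is the less natural reading, and even then a general mention of the outcome would not specify a time-updated last score.

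**Conclusion.** The point holds for the Kaplan-Meier curves and the age-5 and age-10 continence proportions. For these, the stated weights address dropout related to continence or severity only by proxy, and no other named analysis fills the gap. It is a weakness of a sensitivity analysis. It does not show that the primary estimate is biased, nor that the PRO analyses as a whole are unprotected.

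The size cannot be derived from the documents. Under the main set of assumptions, with about half the children lost by age 10, listed-type weights gave 26-31% against a truth of about 24%. Lower loss, weaker dependence or closer proxies would shrink this; the direction depends on which children leave. The conclusion rests on reading the back-reference as the five auxiliaries.

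**What to change.** In Missing data, replace the back-reference with a named covariate list for the weight model, by disease cohort:

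- keep the five listed predictors;
- add the most recent observed BCS (ARM) or BFS (HD) result, updated at each visit from age 3;
- add Krickenbeck category or aganglionosis length, with sparse categories collapsed, and syndromic status;
- add bowel-management status where available;
- for GEE analyses, add the last observed score of the same instrument.

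No new data collection is needed: the scores are annual, severity and syndromic status are structured fields, and eligibility for the bowel-management survey is recorded at each visit.

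The change is not free. At the 70-80% completion expected per visit, 20-30% of current scores will be absent, so some last scores will be old, and there are none before age 3. State how such gaps are handled. A longer covariate list may make the weights variable, above all in the smaller HD cohort, so use stabilised or truncated weights and report their distribution. Say also that the weights still assume dropout depends only on observed history.
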